## Methods: participants, interventions, and outcomes

### Study design

The randomized, open, cross-over clinical trial will be conducted at the Careggi University Hospital, Florence, Italy. A cross-over design will be implemented to allow comparison of a lacto-ovo-vegetarian diet (VD), a Mediterranean diet supplemented with butyrate (MD-Bt), and a Mediterranean diet without any supplement (MD), as control, within the same individual. Participants will act as their own controls in cross-over studies, so individual differences will be controlled for, making the error variance smaller and subsequently reducing the sample size required to find a significant effect due to increased statistical power. The study design follows the Standard protocol items: recommendation for interventional trials (SPIRIT) guidelines (see Fig. 1 and supplementary file #1).

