### Interventions and participant timeline

This clinical randomized study has a cross-over design with three intervention periods and two wash-out periods. After a 2-week run-in period - which will be used to assess participants’ eligibility and to collect demographic details, signed informed consent, and 3-day dietary records - the eligible participants (*N* = 90) will be randomly assigned to follow a 3-month dietary profile with a VD, a MD or a MD-Bt. The VD will contain inulin and resistant-starch-rich foods, eggs, and dairy, in addition to plant-based food, but will not contain meat, poultry, or fish. The MD will contain all the food categories and will provide two portions per week of fish and three portions per week of fresh and processed meat (one of which will consist of fresh or processed red meat). The MD-Bt will be similar to the MD but supplemented with 1.8 g/day of oral butyrate. The three different dietary patterns will be isocaloric and related to the participants’ nutritional requirements, with about 50–55% of energy derived from carbohydrates, < 30% from fats, and 15–20% from proteins. Participants will prepare their meals or eat at restaurants. Alcoholic beverages will be limited to two per day for men and one per day for women. Interventions will be delivered by a dietitian through face-to-face, individual counseling sessions at the Careggi University Hospital. Participants will be provided with a detailed, 1-week menu plan with portions expressed in grams or milliliters as appropriate, and tips and information on the food groups that can be included and those that cannot. The VD plan will also include recipes for preparing meals.

The study design is depicted in Fig. 2. There will be six clinical evaluations of the study population: at baseline before starting the nutritional interventions (T0), 3 months after the onset of the first nutritional intervention (T1), at the end of the first wash-out period, lasting 1.5 months, when individuals will be allowed to resume their normal eating habits, at the onset of the second intervention (T2) at 7.5 months after the onset of the study, at the end of the second nutritional intervention (T3), at the beginning of the third nutritional intervention and at the end of the wash-out period, lasting again 1.5 months (T4), and at the end of the third nutritional intervention (T5).

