### Sample size calculation

Due to the lack of dietary intervention trials on BS and to the fact that gastrointestinal symptoms are quite similar in BS and inflammatory bowel disease, based on a previously published trial [24], a sample size of 80 individuals with BS is required to achieve power of 80% (beta) with alpha = 0.05, to detect a 50-point difference in the mean of SSS (the primary outcome), between VD and MD interventions. We will recruit an extra 10 volunteers (for a total of 90), as we assume that not all individuals would be compliant with the treatments and in case of loss to follow up. Losses will be included in the intention-to-treat but not in the per-protocol analyses.

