### Statistical analysis

The results will be expressed as mean plus/minus SD, median and range, or geometric mean with 95% confidence intervals (CIs) as appropriate. Categorical variables will be presented as frequencies and percentages. All data will be treated as paired samples from a cross-over study. The three interventions will be analyzed combining the results obtained in the three phases of the three groups. Outcomes will be analyzed within each group using the paired comparison Student’s *t* test to test whether the changes are statistically significant. The absolute change (mean baseline value subtracted from mean value after each intervention) will be estimated using the independent samples *t* test.

Raw sequences will be processed in the GM analysis, using a pipeline that combines PANDAseq [25] and QIIME [26]. The UCLUST software [27] will be used to bin high-quality reads into operational taxonomic units (OTUs) at 0.97 similarity threshold through an open-reference strategy. Taxonomy will be assigned through the Ribosomal Database Project (RDP) classifier, using the Greengenes database as a reference. Alpha diversity and rarefaction curves will be computed using different metrics, including the Faith’s phylogenetic diversity, the number of observed OTUs and the Shannon index. Beta diversity will be estimated by weighted and unweighted UniFrac distances, which will be used as input for principal coordinates analysis (PCoA). All statistical analysis will be performed using R and the packages vegan, stats, and made4. The significance of data separation in the PCoA will be tested using a permutation test with pseudo-F ratios (function Adonis in vegan). The Wilcoxon test for paired data will be used to assess significant differences in alpha diversity and taxon relative abundance between groups, and the Kruskal–Wallis test will be used for multiple comparisons. The *p* values will be corrected for false discovery rate (FDR) using the Benjamini-Hochberg method.

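### Changes on the three diets are assigned an independent-samples t test although the same participants supply all of them, so the standard error of the primary VD versus MD contrast is wrong in a direction that the protocol leaves open

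*Protocol article*

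**What the plan says.** The Study design section sets the VD and the MD-Bt against the MD "as control, within the same individual". It justifies the design in these words: "Participants will act as their own controls in cross-over studies, so individual differences will be controlled for, making the error variance smaller", with the further benefit of "subsequently reducing the sample size required to find a significant effect due to increased statistical power". The Interventions and participant timeline section confirms a "cross-over design with three intervention periods and two wash-out periods".

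The Sample size calculation section says that "a sample size of 80 individuals with BS is required to achieve power of 80% (beta) with alpha = 0.05", for a 50-point difference in mean SSS between VD and MD. It relies on a published trial and gives no SD, no correlation and no test. Ten more participants are added, for a total of 90.

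The Statistical analysis section makes four statements in sequence:

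1. "All data will be treated as paired samples from a cross-over study".
2. Results for each diet are combined over the three phases.
3. Before-to-after change within each group is tested with a paired t test.
4. "The absolute change (mean baseline value subtracted from mean value after each intervention) will be estimated using the independent samples" t test.

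**The concern.** The fourth statement conflicts with the first and with the design. After pooling over phases, the VD, MD and MD-Bt data come from the same participants, and an independent-samples t test assumes that they do not. It leaves out the covariance between a person's changes on two diets, so the standard error, p value and confidence interval of the contrast for which the trial was sized do not have their stated properties.

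The paired test that is named does not fill the gap. A before/after comparison within one diet has no comparator, so regression to the mean and spontaneous fluctuation of symptoms would look like a diet effect. The paired Wilcoxon test and the order-adjusted PERMANOVA, which do respect pairing or order, are specified for the microbiota analyses and not for SSS, GAI or BDCAF.

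**Working it through.** **Step 1. Which comparison is meant.** An independent-samples test needs two groups. Change within a diet already has the paired t test, and pooling over phases rules out a comparison of the randomized sequence arms. That leaves diet against diet. This is an inference, since the sentence does not say so.

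**Step 2. Effect on the standard error.** Let a person's changes on two diets have common SD s and correlation rho, with n participants.

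- True variance of the mean difference: 2s²(1 - rho)/n
- Variance used by the independent test: 2s²/n
- Ratio of confidence interval widths (used/true): 1/√(1 - rho)
- True two-sided type I error at nominal 5%: 2[1 - Φ(1.96/√(1 - rho))]

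**Step 3. The plan's own figure.** N = 80 cannot be reproduced without an SD, so it was solved backwards (two-sided alpha 0.05 assumed, 80% power, z sum 2.802):

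- Paired, 80 people: SD of the within-person difference = 50 × √80 / 2.802 = 159.6 (157.7 with the t distribution)
- Independent, 80 changes per diet: SD of change = 50 / (2.802 × √(2/80)) = 112.9
- Parallel, 40 per arm: SD of change = 50 / (2.802 × √(2/40)) = 79.8

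**Step 4. Power if N = 80 was planned as paired.** Hold the SD of the difference at 159.6. The true standard error is 159.6/√80 = 17.85, and 50/17.85 = 2.802. Actual power of the independent test is then Φ(2.802 - 1.96/√(1 - rho)).

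| rho (assumed) | CI width ratio | True type I error | Power of independent test |
|---|---|---|---|
| -0.2 | 0.91 | 7.4% | 84% |
| 0 | 1.00 | 5.0% | 80% |
| 0.2 | 1.12 | 2.8% | 73% |
| 0.3 | 1.20 | 1.9% | 68% |
| 0.5 | 1.41 | 0.56% | 51% |

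A simulation with t tests (20,000 runs, n = 80, SD of difference 157.7) gave power 68.4% and 51.9%, and type I error 2.1% and 0.65%, at rho 0.3 and 0.5.

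**Step 5. Power if N = 80 came from a 40-per-arm parallel formula.** With SD of change 79.8 and 80 people on both diets, the standard error at rho 0 is 79.8 × √(2/80) = 12.6, and power is Φ(50/12.6 - 1.96) = 97.7% with either test. It is higher at each positive rho tried, up to 0.8.

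**Step 6. What rho could be.** The Outcome measures section takes change from the beginning to the end of each intervention, so each period has its own baseline.

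- If all of a person's scores share one correlation r, the covariance of two such changes is proportional to r - r - r + r = 0, so rho = 0.
- If correlation decays with time, rho can be negative. As an illustration, assume r(t) = 0.7^(t/3 months), with two adjacent 3-month periods separated by 1.5 months. Then rho = [2(0.586) - 0.837 - 0.410] / [2(1 - 0.7)], about -0.125, and the type I error is about 6%.
- If some people respond to any diet, rho is positive. The GAI, which rates every period against the time before study entry, also makes positive correlation plausible for that outcome.

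**The case against.** Three stronger conclusions are tempting, and the documents support none of them.

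- **A reader might infer that the test must be conservative and its interval too wide.** That needs a positive rho between changes. Subtracting each period's baseline already removes the stable personal level, so rho may be zero or negative (Step 6). Much of the own-control benefit claimed in the Study design section survives that subtraction, whichever t test follows.
- **A reader might infer that 80 participants can be right for only one of the two treatments of the data.** At rho 0 both hold together: 112.9 × √2 = 159.6.
- **A reader might infer that the stated 80% power depends on pairing and is therefore lost.** The Study design rationale points towards pairing, but the Sample size calculation section does not say which formula was used. Under the parallel formula nothing of practical size is lost (Step 5).

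It is also fair that the quoted sentence does not mention diets, and that a simple paired comparison of each person's changes would be enough to remove the contradiction.

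These objections limit what can be said about direction and size. They do not rescue the test: it is stated rather than left open, and it contradicts the pairing commitment in the same section.

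**Conclusion.** The concern holds as an error in the stated analysis. The independent-samples t test breaks its own assumption on the contrast for which the trial was sized, and contradicts both the Study design section and the opening of the Statistical analysis section. Confidence in this is high, subject to the between-diet reading in Step 1.

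The consequence is conditional. The test is conservative if rho is positive, has the correct standard error if rho is zero, and is anti-conservative if rho is negative. Any loss of power depends both on rho and on how N = 80 was derived, and neither is given. N = 80 is therefore neither confirmed nor refuted, and it should not be concluded that the trial is underpowered.

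**What to change.** - **Test.** Replace the independent-samples t test for SSS and the other continuous outcomes with a within-person between-diet analysis. At minimum this is a paired contrast of each person's results on two diets. A linear mixed model for end-of-period values is preferable, with diet, period and sequence as fixed effects, the period baseline (T0, T2 or T4) as covariate and a random participant effect. It also handles treatment order, which the clinical analysis as written does not.
- **Why the model is worth having even at rho 0.** If all of a person's scores are equally correlated (an assumption), a within-person contrast of end-of-period values has variance 2σ²(1 - r)/n, against 4σ²(1 - r)/n for the contrast of changes. Where the change contrast has 80% power, this one has Φ(2.802 × √2 - 1.96), about 98%.
- **Reporting.** Give VD minus MD and MD-Bt minus MD with 95% confidence intervals. Keep the before/after tests as description.
- **Sample size.** Restate the sentence with the test assumed and the SD of the within-person difference behind N = 80.

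The cost is wording and analyst time. The period baselines are already collected, and no extra visits or participants are needed.

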#### Compliance

Compliance with the interventions will be achieved using behavior change strategies including self-monitoring, and regular phone calls for dietary counseling. In particular, participants will receive at least one unannounced phone call during each intervention, in which participants will recall his or her 24-h diet period. Furthermore, participants will be provided with a detailed one-week menu plan for each dietary period with all foods expressed in weight and/or volume measures, and a hand-out containing details on their assigned diet, including food groups that can be included and ones that should be avoided. The vegetarian menu plan will also include recipes for preparing meals. Participants may discontinue the intervention or withdraw from the study for the following reasons: (1) at the request of the participant; (2) if the investigator considers that a participant’s health will be compromised due to adverse events or concomitant illness that develop after entering the study. Participants prematurely discontinued from the study before the 3-month evaluation will have the baseline clinical and laboratory evaluations performed.

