Before starting the data analysis, the level, pattern and likely causes of the missingness in the baseline variables and outcomes will be investigated by preparing appropriate tables. This information will be used to determine whether the level and type of missing data has the potential to introduce bias into the analysis results or substantially reduce the precision of estimates for the proposed statistical methods. Sensitivity analyses will be undertaken, based on the assumption that missing outcomes are the worst possible, or the best possible, in different randomization groups. If these show that conclusions may differ based on missing values, then supplementary multiple imputations for missing values will be undertaken. These analyses will account for results of any losses to follow up insofar as they pertain to differences in measured variables (i.e. under the assumption of missing at random). Finally, subgroup analyses will be performed to analyze possible differences in the changes according to some characteristics of the study population, such as age, sex, categories of BMI, and physical activity. A *p* value <0.05 will be considered statistically significant. Statistical analyses will be performed using SPSS software for Macintosh (SPSS Inc., Chicago, IL, USA).

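### Best/worst values for missing outcomes are set by randomisation group rather than by diet, they decide whether multiple imputation is run, and the main t tests are available-case despite the intention-to-treat statement

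*Protocol article*

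**What the plan says.** The Statistical analysis section of the protocol article sets out missing-data handling in stages. The level, pattern and likely causes of missingness are tabulated first. Then: "Sensitivity analyses will be undertaken, based on the assumption that missing outcomes are the worst possible, or the best possible, in different randomization groups". Then: "If these show that conclusions may differ based on missing values, then supplementary multiple imputations for missing values will be undertaken". The imputation is stated to work under missing at random.

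The same section gives the main tests for the clinical outcomes: a paired t test of start against end, and an independent samples t test on the absolute change. Results for each diet are pooled over the three phases of the three groups. Recruitment and randomization describes 1:1:1 allocation to three arms, and Interventions and participant timeline describes three intervention periods with two wash-outs.

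On the analysis population, Sample size calculation states: "Losses will be included in the intention-to-treat but not in the per-protocol analyses".

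**The concern.** Three features of these rules work against each other.

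- **Unit of the extremes.** The question is about diets, but the extremes are assigned to randomised groups. In a cross-over each such group passes through every diet, so setting one group to worst and another to best does not set one diet against another.
- **Gate.** Multiple imputation is the only analysis that is explicitly valid under missing at random, and it is run only if the extreme-value check suggests that conclusions may differ. Whether it is run therefore turns on how one undefined phrase is read.
- **Main result.** A t test on change cannot use a phase without an end value. The main result is available-case, while another section says that losses are included.

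The diets are open to participants and the trial runs about 12 months (3 x 3 months of diet plus 2 x 1.5 months of wash-out). The sample size section itself expects some non-compliance and loss. Loss that depends on the diet is plausible, and it is the case a sensitivity analysis should address directly.

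**Working it through.** **Inputs.** 90 participants randomised 1:1:1, of whom 80 are required and 10 are added for non-compliance and loss (Sample size calculation; Recruitment and randomization). SSS range 0 to 600 (Primary outcomes). Target difference 50 points. No standard deviation is stated.

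**1. The plan's own figures.** The plan states that "a sample size of 80 individuals with BS is required to achieve power of 80% (beta) with alpha = 0.05". Without an SD the 80 cannot be reproduced. If the comparison is paired and two-sided, n = (SDdiff x (1.960 + 0.842)/50)^2, so n = 80 implies SDdiff = 50 x sqrt(80)/2.802 = 159.6. That value is used below only to calibrate a simulation. The 90 is coherent: 80/(1 - 10/90) = 90.

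**2. What the literal rule does.** Take a participant lost in the first phase, with no end SSS on any diet.
- Extremes by group: VD and MD both get 600, or both get 0. The VD-MD difference in end score is 600 - 600 = 0 or 0 - 0 = 0.
- Extremes by diet: the difference is 600 - 0 = +600 or 0 - 600 = -600.

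Under the literal rule, only people who miss exactly one of VD and MD move the contrast to any extent.

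**3. Size of the extremes.** With m end values missing on a diet out of 90, going from best to worst moves that diet's mean by m/90 x 600.
- Upper end, all 10 missing on the same diet: 10/90 x 600 = 66.7 points.
- Losses spread evenly over 0, 1 or 2 completed phases (assumption): each lost person misses on average (3 + 2 + 1)/3 = 2 phases, so 10 x 2/3 = 6.7 values per diet are missing, and 6.7/90 x 600 = 44 points.
- If the values are missing on both VD and MD, the two opposite by-diet scenarios lie twice as far apart: 133 points at the upper end, 89 with spread losses.

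**4. How often the gate would open.** Simulation with 1000 runs per row. All of the following are assumptions: three sequences forming a Latin square, SD of change 112.8 per diet with uncorrelated changes (SDdiff 159.6), start SSS mean 250 and SD 80, and loss timing as in step 3. The comparison is a paired VD-MD t test on change. The gate opens when any best/worst scenario gives a conclusion different from the available-pairs result.

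| Lost | True VD-MD | Mean difference, extremes by diet | Mean difference, extremes by group | Gate opens, by diet | Gate opens, by group |
|---|---|---|---|---|---|
| 10 | -50 | -91.1 to -3.0 | -61.9 to -32.2 | 98% | 53% |
| 10 | 0 | -43.9 to 44.7 | -14.7 to 15.6 | 90% | 23% |
| 5 | -50 | -71.3 to -26.8 | -56.4 to -41.6 | 73% | 25% |
| 5 | 0 | -22.7 to 22.1 | -7.6 to 7.1 | 34% | 11% |

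**5. What the main tests keep.** With 10 lost on the same timing, about 83 values per diet (90 - 6.7) and about 81 VD-MD pairs remain. About 10/3 = 3.3 of the lost people have no post-baseline value and contribute nothing.

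**The case against.** The strongest reply is that this is a recognisable staged plan: describe the missingness, bound it with extremes, then impute. It has several parts.

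- **Randomisation groups may be loose wording for diets.** Participants are described as assigned to a diet, and the microbiota paragraph uses groups for paired comparisons. This is possible, but the text does not say so, and the step 4 figures show that the reading matters.
- **Read by diet, the gate often opens, so imputation is usually run.** This stands as far as it goes, but a gate that opens in 90% to 98% of trials with 10 lost filters little. With 5 lost it opens in 34% to 73%, so almost always would be too strong.
- **Read by sequence, the contrast is still moved.** This also stands: the simulated difference ranged from -62 to -32. The stress is indirect, not absent.

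A reader might go further than the document allows in four ways.

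- That the losses cannot enter the analysis at all, or that the estimate rests on people who tolerated every diet. Neither is so: someone lost in the third phase still supplies two diets.
- That there is no usable check. The tabulation, the extremes and the conditional imputation are checks.
- That 10 missing values are what the plan expects. The extra 10 also cover non-compliers, who may well have outcome data.
- That people stopping in the second or third phase get no exit evaluation, because the Compliance section says only: "Participants prematurely discontinued from the study before the 3-month evaluation will have the baseline clinical and laboratory evaluations performed". Silence on later phases in a condensed article is not evidence that the full protocol lacks a rule.

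**Conclusion.** The point holds in a limited form. As worded, the best/worst rule is indexed to the sequence rather than the diet, so it under-stresses the comparison the trial is sized for; if diets are meant, the wording is wrong. The only missing-at-random analysis is made conditional on that rule. The stated main analysis is available-case and does not deliver the intention-to-treat statement for missing phases or for people with no post-baseline value.

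The arithmetic on the 0 to 600 range needs no SD. Going from best to worst moves a diet mean by up to 67 points if all 10 lack that diet's end value, and by about 44 if losses are spread, against a target of 50. The 67 therefore exceeds the target only at the upper end. The gate rates depend on the assumed SD, start scores, sequences and timing of loss.

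This should be changed before analysis. It does not show that the results will be biased.

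**What to change.** 1. **Main analysis.** Make the main intention-to-treat analysis a mixed model with diet, period and sequence as fixed effects and participant as a random effect, using every completed period of every randomised participant. It is valid under missing at random.
2. **Sensitivity analysis.** Replace extremes by randomisation group with graded deltas added to SSS values missing under VD, MD or MD-Bt, varied separately by diet up to the point where the conclusion changes. Run it whatever the other results show. Graded deltas stay informative where extremes do not: with 6.7 of 90 missing, a delta of 50 points moves a diet mean by 6.7/90 x 50 = 3.7 points.
3. **Wording.** Change the sentence on losses in Sample size calculation so that it matches: all randomised participants belong to the intention-to-treat population and enter through their completed periods. Say how people with no post-baseline value are handled. A model on change does not bring them in either, so they enter through the sensitivity analysis.

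The cost is a few sentences and some extra programming, with no change to visits or clinical management. The downside is that the main model relies on missing at random, which is why the by-diet sensitivity analysis should be unconditional.
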